#### Strategies to improve adherence to interventions {11c}

Adherence to the protocol procedures will be recorded daily in the electronic case report forms during the first 14 days of the study. A document summarizing the study protocol (Additional file 5) and each procedure to adjust mechanical ventilation and ARDS adjunctive therapy will be provided to the investigators, allowing availability at the bedside of the study procedures.

#### Relevant concomitant care permitted or prohibited during the trial {11d}

Patients in both groups will receive deep sedation (i.e., targeting RASS score between − 3 and − 4) after randomization. After a successful deep sedation weaning trial, patients in both groups will be ventilated with VT 6–8 mL kg^−1^ PBW, sedation dose adjusted to target a RASS score between − 2 and 0, and tested daily with a spontaneous breathing test until successful extubation. All ventilatory co-interventions will be standardized to ensure group comparability:
Neuromuscular blocking agent use will be advocated during the first 48 h of ARDS, in case of persisting severe hypoxemia (PaO_2_/FiO_2_ < 100 mmHg with a PEEP > 10 cmH_2_O) or in case of ventilator asynchrony despite deep sedation in assist volume-controlled mode (Table 1).Prone position will be advocated as long as PaO_2_/FiO_2_ < 150 mmHg or PEEP > 10 cmH_2_O or FiO_2_ > 60% in the supine position.Extracorporeal membrane oxygenation (ECMO) will be considered if PaO_2_/FiO_2_ < 60 mmHg in the prone position.ECCOR will be considered in patients with persisting severe respiratory acidosis despite adjustments of the ventilatory settings and pharmacological interventions as defined in Table 1.Recruitment maneuvers will not be recommended.

#### Provisions for post-trial care {30}

None

### Outcomes {12}

#### Primary outcome

The primary outcome is a composite score based on 90-day all-cause mortality as the first criterion and the number of VFD at day 60 after inclusion as the second criterion. The composite score will be obtained by comparing each patient of one group to all patients of the other group. For each pair, a value of + 1 (favorable), − 1 (unfavorable), or 0 (neutral) will be given to each patient. The score will be built as follows:
A value of + 1 will be given for a patient alive at day 90 paired with a patient deceased at day 90.A value of + 1 will be given for a patient alive at day 90 paired with a patient alive at day 90 but with a lower number of VFD.A value of 0 will be given for pairs with both patients deceased at day 90.A value of 0 will be given in case of an identical number of VFD for the pairs of patients alive at day 90.A value of − 1 will be given for a deceased patient in comparison with patients alive at day 90.A value of − 1 will be given for a patient alive at day 90 paired with a patient alive at day 90 but with a higher number of VFD.

For a given patient, the score will correspond to the sum of values resulting in the comparison to all patients of the other group.

VFD will be computed as follows from the day of inclusion:
VFD = 0 if the patient dies between inclusion and day 60VFD = 60 − *x* if the patient is successfully weaned from invasive mechanical ventilation, with *x* being the number of days from inclusion to last successful extubation. Successful weaning from mechanical ventilation will be defined as extubation without reintubation within at least 48 h (or weaning from mechanical ventilation for at least 48 h for patients with tracheostomy)VFD = 0 if the patient is mechanically ventilated for more than 60 days after inclusion

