### Sample size {14}

The sample size was computed through data simulations based on the following hypotheses:
Ninety-day mortality 45% in the control group, and 40% in the intervention group (i.e., relative reduction 11%)Mean ± standard deviation (*SD*) VFD at day 60 28 ± 16.5 in the control group and 34.5 ± 13 in the intervention group

The expected mortality in patients with COVID-19 and moderate to severe ARDS is between 34 and 50% [1]. The mean and *SD* of VFD at day 60 in the control group was taken from the subgroup of patients with PaO_2_/FiO_2_ < 150 mmHg included in the control group of the prospective randomized Xtravent-study comparing ultra-protective ventilation with extracorporeal CO_2_ removal versus conventional protective ventilation [7]. To be conservative, we have chosen to take an expected difference between the two groups of the present study corresponding to 50% of the difference observed in the Xtravent-study between the control and the intervention groups.

For each scenario corresponding to a given sample size, 1000 datasets were simulated. For each simulation, the score was computed for each patient and compared between the two groups using the test of Mann and Whitney. The power was computed as the proportion of tests with a bilateral *p*-value < 0.05.

The results of the simulations allowed us to determine that the inclusion of 100 patients per group will achieve a power greater than 80% to conclude a significant difference between the groups.

The simulations were implemented by two biostatisticians with the SAS software, version 9.4 (Copyright (c) 2002–2003 by SAS Institute Inc., Cary, NC, USA) and the R software, version 3.6.1 (R Core Team (2012)). The results were similar.

To account for premature exits from the study (withdrawal of informed consent for example), we have planned to add 10% more patients (10 supplementary patients in each group for a total of 220 patients).

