#### Analysis of the primary outcome

The main analysis will be carried out by intention to treat, i.e., all the patients included in the study will be analyzed in their initial randomization group regardless of whether the allocated ventilation strategy was effectively applied or not.

The distribution of the composite score will be described in each group using the following statistics: mean, standard deviation, quartiles, and minimum and maximum values. It will be compared between the two groups using the test of Mann and Whitney.

The ULTV effect size will be quantified by the probability of a favorable result for a patient belonging to the ULTV arm in comparison with a patient belonging to the protective ventilation arm. This probability will be estimated by the proportion of pairs for which the patient of the ULTV arm will have a favorable result [20]. This estimate will be given with a 95% confidence interval.

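### The primary score compares patients only with the opposite arm, so a Mann-Whitney test on it rejects about 88% of the time at nominal 5% when there is no treatment effect (100 per arm, 45% mortality)

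*Protocol article*

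**What the plan says.** The Primary outcome section (Outcomes {12}) defines the pairing: "The composite score will be obtained by comparing each patient of one group to all patients of the other group". Each pair gives +1, 0 or −1, with 90-day survival first and ventilator-free days (VFD) second. The patient-level score follows: "For a given patient, the score will correspond to the sum of values resulting in the comparison to all patients of the other group". Two deaths are meant to be neutral: "A value of 0 will be given for pairs with both patients deceased at day 90".

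Analysis of the primary outcome then fixes the test on this score: "It will be compared between the two groups using the test of Mann and Whitney".

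Sample size {14} says the power simulation did the same: "the score was computed for each patient and compared between the two groups using the test of Mann and Whitney". It continues: "The power was computed as the proportion of tests with a bilateral" p-value below 0.05. The inputs are "Ninety-day mortality 45% in the control group, and 40% in the intervention group" and VFD of "28 ± 16.5 in the control group and 34.5 ± 13 in the intervention group". The stated result is power above 80% with 100 patients per group.

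None of these sections mentions a permutation reference, scoring against both arms, or a check of the type I error.

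**The concern.** The Mann-Whitney null distribution requires the values being ranked to be exchangeable between arms when treatment does nothing. Scores built only from the opposite arm are not. ULTV patients are measured against the control sample, and control patients against the ULTV sample. Any chance difference between the two samples enters both sets of scores, with opposite signs.

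- **Deaths.** Every dead ULTV patient scores minus the number of control survivors, and every dead control patient scores minus the number of ULTV survivors. If the survivor counts differ by one, the large block of tied deaths splits completely in one direction. This defeats the protocol's own rule that a pair of deaths is neutral.
- **Survivors.** A chance shift in VFD raises the scores in one arm and lowers them in the other, which roughly doubles the test statistic.

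This is the trial's only primary test. If its error rate is not controlled, the trial can declare benefit or harm of a ventilation strategy by chance.

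**Working it through.** **Inputs.** From Sample size {14}: 100 per group; 90-day mortality 45% (control) and 40% (ULTV); VFD 28 ± 16.5 and 34.5 ± 13; two-sided 0.05. Assumptions not in the document: the VFD mean and SD describe survivors, and survivor VFD is normal, clipped to 0–60 and rounded to days. Beta, unclipped and unrounded versions were also run.

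**Tests compared on the same simulated data.**

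- (a) Protocol: score of patient i = Σ sign(outcome i − outcome j) over j in the other arm, then Mann-Whitney.
- (b) Mann-Whitney on the ordered outcome (death by day 90 lowest and tied, then VFD).
- (c) As (a), but with j running over all patients of both arms. This score equals 2 × midrank − (N + 1), so (c) must give the same result as (b), and it did.

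**Step 1: reproduce the plan's figure.** Under the plan's alternative, (a) rejects in 81.3% of 10,000 runs (80–82% across VFD shapes), which matches the stated power above 80%. On the same data (b) and (c) reject in 38% (37–40% across shapes). The stated power appears only with the opposite-arm score, so the text has been read as the simulation was done.

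**Step 2: no treatment effect** (VFD 28 ± 16.5 in both arms, 100 per arm).

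| Mortality in both arms | (a) protocol | (b)/(c) one scale |
|---|---|---|
| 0% | 30% | 4.7% |
| 20% | 35% | 4.7% |
| 34% | 60% | 5.5% |
| 40% | 78% | 4.1% |
| 45% | 87.6% (10,000 runs) | 5.0% |
| 50% | 93% | 5.1% |

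The other rows are 2,000 runs each; repeat runs differed by a few points (for example 60–64% at 34%). At 45% the rejections split into about 43% for ULTV and 44% for control. The SD of the standardised statistic is 3.6 where it should be 1. The problem grows with sample size: 91% at 110 per arm and 96% at 200 per arm. Dividing each score by the size of the opposite arm does not help (88% with equal arms, 92% with 98 and 102 patients).

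**Step 3: one case by hand.** Take 45 ULTV deaths and 46 control deaths out of 100 each, with survivors' VFD evenly spread over 0–60 in both arms. Death scores are −54 (ULTV) and −55 (control). The Mann-Whitney U for ULTV, with expectation 5,000, is built as follows.

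| Pairs | Ordered outcome | Protocol score |
|---|---|---|
| ULTV alive, control dead: 55 × 46 | 2,530 | 2,530 |
| Both dead: 45 × 46 = 2,070 | 1,035 (tied, half) | 2,070 (all to ULTV) |
| Both alive: 55 × 54 = 2,970 | 1,485 | 1,511.5 |
| ULTV dead, control alive | 0 | 0 |
| **U** | **5,050** | **6,111.5** |

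The tie-corrected null SD of U is 389.5 for the ordered outcome and 404.4 for the protocol score. With the 0.5 continuity correction:

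- Ordered outcome: z = 49.5 / 389.5 = 0.13, p = 0.90.
- Protocol score: z = 1,111 / 404.4 = 2.75, p = 0.006.

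Of the difference in U, 1,035 of 1,061.5 comes from the pairs that the protocol calls neutral.

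**Step 4: what drives it.** In null trials at 45% mortality, rejection was below 2% when the two death counts happened to be equal and about 93–94% when they differed at all.

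**Step 5: a further sign that the test is not valid.** Rejection is lower under the plan's assumed benefit (81–82%) than under no effect (88%), and about 6% of trials simulated with benefit reject in favour of control.

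**The case against.** Four points can be made for the plan.

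- **The 88% is one scenario.** This stands. It belongs to 45% mortality and 100 per arm. At the low end of the protocol's range (34%) the rate is about 60%, so a false claim is then more likely than not rather than nearly certain. No scenario at 100 per arm comes near 5%.
- **Death imbalance is not the whole story.** This also stands. With no deaths the test still rejects about 30% of the time, so survivors' VFD contributes to the direction too.
- **The effect estimate may be sound.** Analysis of the primary outcome also reports the proportion of pairs favourable to ULTV, with a 95% confidence interval. That proportion comes straight from the pairs and does not depend on the Mann-Whitney null variance. The defect is in the p-value, and nothing here shows the proportion to be wrong.
- **The analysis plan, not shown, may use a permutation reference.** This does not rescue the text. The protocol names both the score and the test, in the analysis section and again for the power simulation, and says twice that comparison is with the other group. The match to the stated power supports the literal reading.

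Sample size {14} does not say which VFD distribution was used, or whether the mean and SD refer to survivors. Scaling survivors' means to 50.9 (28 / 0.55) and 57.5 (34.5 / 0.60), as if the stated means included deaths, gives 82% with the protocol's method and 40% with the valid one, so the conclusion does not change.

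**Conclusion.** The concern holds. As written, the primary test has no usable control of type I error: about 88% at nominal 5% with 100 per arm and 45% mortality, about 60% to 93% over the expected mortality range of 34% to 50%, and about 30% with no deaths. False claims of benefit and harm are about equally likely. These rates rest on simulation with equal arms and independent patients, and they hardly move with the shape of the VFD distribution. The stated power above 80% is a product of the same fault; a valid test has about 38%. This must be fixed before the primary analysis is run.

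**What to change.** Keep the endpoint and the pairwise rules. In Primary outcome, Analysis of the primary outcome and Sample size {14}, replace scoring against the other group with either of two equivalent forms:

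- score each patient against all other randomised patients of both arms (Finkelstein-Schoenfeld scoring) and compare these scores between arms; or
- rank all patients on one scale (death by day 90 lowest and tied, then VFD from 0 to 60) and apply the tie-corrected Mann-Whitney test.

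The proportion of favourable pairs and its confidence interval can stay as the effect measure. Stratifying the test by centre would be a separate choice and is not needed for this repair.

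The wording and code change is small and needs no new data. The real cost is the sample size. Under the plan's own assumptions a valid test needs about 285 per group for 80% power (79% at 280, 82% at 290). That is about 570 patients, or 570 × 1.1 = 627 with the plan's 10% allowance, against the 220 planned. If recruitment cannot be extended, the protocol should state the power of about 38% openly. The change should be documented before anyone sees results by arm.

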#### Secondary outcomes

Ninety-day all-cause mortality.VFD at day 60 after inclusion.Time from inclusion to successful extubation.Successful extubation will be defined as extubation without reintubation or death within 48 h in intubated patients and as weaning of invasive mechanical ventilation for at least 48 h in tracheotomized patients.Length of hospital stay from inclusion.Value of respiratory parameters (PaO_2_/FiO_2_ ratio, pH, PaCO_2_, PEEP, VT, total PEEP, plateau pressure, driving pressure, respiratory rate, MP) assessed daily from inclusion to weaning of deep sedation or 14 days after inclusion whichever comes first.Total PEEP and plateau pressure will be measured at the end of 3-s end-expiratory and end-inspiratory pauses, respectively. Driving pressure will be defined as the difference between plateau pressure and total PEEP. MP will be computed as previously described [14], and partitioned into 3 components:
$$ VT-\mathrm{related}\ \mathrm{MP}=0.0098\times RR\times {VT}^2\times \frac{1}{2}{El}_{rs} $$
$$ \mathrm{PEEP}-\mathrm{related}\ \mathrm{MP}=0.0098\  RR\times VT\times {\mathrm{PEEP}}_{\mathrm{tot}} $$
$$ \mathrm{Resistive}\ \mathrm{MP}=0.0098\times {RR}^2\times {VT}^2\times \frac{\left(1+I:E\right)}{60\times I:E}{R}_{\mathrm{aw}} $$

with RR = respiratory rate, *El*_*rs*_ = elastance of the respiratory system = driving pressure/VT, *I:E* = inspiratory-to-expiratory ratio, *R*_aw_ = airway resistance = (peak airway pressure − plateau pressure)/inspiratory flow.
6.Value of daily sedation dose (midazolam, propofol, and opioid) during the first 14 days after inclusion.Opioid doses will be expressed as morphine equivalent (1 mg fentanyl = 100 mg morphine, 1 mg sufentanil = 1000 mg morphine).7.The use of rescue therapy (i.e., muscle relaxant, prone position, inhaled nitric oxide, recruiting maneuvers, ECMO) during the first 14 days after inclusion.8.Severe mixed acidosis, ventilator-associated pneumonia, acute cor pulmonale, barotrauma, and any serious adverse events during the first 28 days after inclusion.Severe mixed acidosis will be defined as the association of pH < 7.15 and PaCO_2_ > 45 mmHg.Ventilator-associated pneumonia will be reported as clinically diagnosed by the attending physician.Acute cor pulmonale will be defined as the association of right ventricle dilatation (right ventricle surface/left ventricle surface > 0.6) and septal dyskinesia assessed by echocardiography.Barotrauma will be defined as the occurrence of any pneumothorax, pneumomediastinum, subcutaneous emphysema, or pneumatocele of more than 2 cm.Serious adverse event will be defined as any adverse event resulting in death, leading to a life-threatening condition, resulting in hospitalization or prolongation of hospitalization, resulting in disability or permanent damage, and resulting any other important medical event.9.Montreal Cognitive Assessment (T-MoCA) test [15] assessed by a phone call at day 365 after inclusion.10.SF-36 score [16] assessed by a phone call at day 365 after inclusion.11.IES-R score [17] assessed by a phone call at day 365 after inclusion.12.Incremental cost-effectiveness ratios of the innovative strategy compared to the reference strategy at day 90 after inclusion.

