#### Intervention description {11a}

Within the first hour after randomization, the control group will be managed with protective ventilation (i.e., VT 6 mL kg^−1^ PBW, PEEP set using the PEEP-FiO_2_ table of the low PEEP arm of the ALVEOLI trial [10], aiming for a plateau pressure < 30 cmH_2_O) under deep sedation (i.e., Richmond Agitation-Sedation Scale (RASS) score [13] between − 3 and − 4). Respiratory rate (RR) will be set targeting a pH range between 7.20 and 7.45, and VT may be increased if pH remains below 7.15 despite a RR set to 35 min^−1^ and minimization of instrumental dead space (Table 1).

**Table 1 Tab1:** Summary of the ventilation procedure

• Ventilatory mode: volume-assist control.	
• Instrumental dead space: minimize by using a heated humidifier and a low-volume endotracheal tube connector.	
• Control group: set VT to 6 mL kg^−1^ PBW.	
• Intervention group: stepwise reduction by 1 mL kg^−1^ PBW steps at intervals ≤ 2 h down to 4 mL kg^−1^ PBW and increase RR up to 35 min^−1^ to maintain VE constant.	
• Ratio of the duration of inspiration to the duration of expiration: adjust between 1:2 and 1:4 to maintain intrinsic PEEP ≤ 2 cm H_2_O.	
• Ventilatory goals: plateau pressure ≤ 30 cmH_2_O; 60 ≤ PaO_2_ ≤ 80 mmHg or 88% ≤ SpO_2_ ≤ 95%; 7.20 ≤ pH ≤ 7.45.	
• Allowable combinations of PEEP (cm of H_2_O) and FiO_2_: 5 and 30%, 5 and 40%, 8 and 40%, 8 and 50%, 10 and 50%, 10 and 60%, 10 and 70%, 12 and 70%, 14 and 70%, 14 and 80%, 14 and 90%, 16 and 90%, 18 and 90%, 20 and 100%, 22 and 100%, and 24 and 100%. Other combinations are allowed as a function of hemodynamic tolerance to PEEP.	
• Set ventilator alarms as follows: upper VT alarm set to 1.5 × set VT to identify double-triggering, upper RR alarm set to 37 min^−1^.	
• Procedure when PaO_2_ < 60 mmHg or SpO_2_ < 88% despite adjustments of FiO_2_ and PEEP (in the following order as needed): 1, use PP; 2, add NMBA; 3, add iNO; and 4, consider ECMO.	
• Procedure when PaO_2_ > 80 mmHg or SpO_2_ > 95% (in the following order as needed): 1, stop iNO; 2, stop NMBA if administration > 48 h; and 3, adjust FiO_2_ and PEEP.	
• Procedure when plateau pressure is > 30 cmH_2_O (in the following order as needed): 1, inject a bolus of NMBA; 2, reduce VT to 4 mL kg^−1^ PBW (if pH ≥ 7.20); and 3 decrease PEEP down to a minimum of 5 cmH_2_O.	

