### Methods for additional analyses (e.g., subgroup analyses) {20b}

Exploratory analysis regarding the primary outcome will be performed by comparing both arms of the study in the following subgroups of patients: age greater or lower than its median value, SAPS2 greater or lower than its median value, SOFA score at randomization greater or lower than its median value, renal SOFA at randomization < 2 and ≥ 2, bicarbonates at randomization < 22 and ≥ 22 mmol L^−1^, driving pressure at randomization greater or lower than its median value, plateau pressure at randomization greater or lower than its median value, compliance of the respiratory system at randomization greater or lower than its median value, mechanical power at randomization greater or lower than its median value, PaO_2_ at randomization ≤ 100 mmHg and > 100 mmHg, and pH at randomization greater or lower than its median value.

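### The three mechanical-power formulas use a constant, 0.0098, that fits neither litres nor millilitres with pressures in cmH2O, and no units are stated

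*Protocol article*

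**What the plan says.** In the protocol article, Outcomes {12}, Secondary outcomes, MP is one of ten respiratory parameters assessed daily until weaning of deep sedation or day 14. The article states that "MP will be computed as previously described [14], and partitioned into 3 components". The components are VT-related, PEEP-related and resistive.

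- The VT-related component contains "0.0098\times RR\times {VT}^2\times \frac{1}{2}{El}_{rs".
- The PEEP-related component is 0.0098 times respiratory rate (RR), VT and total PEEP.
- The resistive component begins with "0.0098\times {RR}^2\times {VT}^2", followed by (1 + I:E)/(60 × I:E) and airway resistance.

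Elastance is defined as "elastance of the respiratory system = driving pressure/VT", and resistance as peak minus plateau pressure, divided by inspiratory flow. No units are printed for VT, resistance or MP.

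Elsewhere pressures are in cmH2O ("aiming for a plateau pressure < 30 cmH_2_O"), RR is per minute ("increase RR up to 35 min^−1^ to maintain VE constant"), and VT appears only in mL per kg of predicted body weight (PBW). MP is also a subgroup variable in section {20b}: "mechanical power at randomization greater or lower than its median value".

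**The concern.** The leading constant has one job: to turn volume times pressure into joules, so that multiplying by RR gives joules per minute. Its value is fixed by the units of volume and pressure, and the printed value does not match the units a reader would use.

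Section {20a} describes quantitative secondary outcomes by mean and standard deviation or quartiles, with minimum and maximum. If the formulas are applied as printed, each of those figures for MP, and each between-arm difference, is on the wrong scale and cannot be compared with MP reported elsewhere. Because the units are not stated, a reader cannot tell from the article which scale was meant.

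**Working it through.** **1. The constant from first principles.** 1 cmH2O = 98.0665 Pa.

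| Volume unit | J per (volume unit × cmH2O) | Ratio to 0.0098 |
|---|---|---|
| litre (0.001 m³) | 0.0980665 | 10.007 |
| decilitre | 0.00980665 | 1.0007 |
| millilitre | 0.0000980665 | 0.010007 |

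The printed value fits decilitres with cmH2O, or litres with mmH2O. The article uses neither pair.

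**2. Is the rest of the algebra sound?** Inspiratory time in seconds is (60/RR) × I:E/(1 + I:E). Constant inspiratory flow is therefore VT × RR × (1 + I:E)/(60 × I:E). Multiplying by resistance, VT and RR gives the printed resistive term. The elastic term (half of VT² × elastance) and the PEEP term (VT × total PEEP) are also correct. Nothing in the formulas offsets the constant.

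**3. Worked example, VT in litres.** Assumed inputs, not from the article: VT 0.4 L, RR 25 per minute, driving pressure 12 cmH2O, total PEEP 10 cmH2O, resistance 12 cmH2O/L/s. I:E is 1:2, within the article's instruction to "adjust between 1:2 and 1:4 to maintain intrinsic PEEP ≤ 2 cm H_2_O". Elastance = 12/0.4 = 30 cmH2O/L.

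| Component | With 0.098 | As printed (0.0098) |
|---|---|---|
| VT-related: c × 25 × 0.16 × ½ × 30 | 5.88 | 0.588 |
| PEEP-related: c × 25 × 0.4 × 10 | 9.80 | 0.980 |
| Resistive: c × 625 × 0.16 × (1.5/30) × 12 | 5.88 | 0.588 |
| Total | 21.56 J/min | 2.156 |

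**4. Check against direct integration.** Pressure times flow was integrated over a constant-flow breath in SI units for 18 assumed scenarios: PBW 50, 65 or 80 kg; VT 6 mL/kg at RR 25 or 35, or 4 mL/kg at RR 35; I:E 1:2 or 1:4; PEEP 10; resistance 12; driving pressure 10 to 20. The integrated power was 10.007 times the printed total in every scenario. Printed totals ran from 1.32 to 6.06, against 13.18 to 60.63 J/min. The excess of 0.007 over 10 is only the rounding of 0.0980665 to 0.098.

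**5. Other units for VT.** Take PBW 65 kg, VT 6 mL/kg = 390 mL, RR 25, driving pressure 14 and PEEP 10. The elastic and PEEP terms together should be 0.0980665 × 25 × 0.39 × (7 + 10) = 16.25 J/min.

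- VT in mL: 0.0098 × 25 × 390 × 17 = 1624, about 100 times too large.
- VT in mL/kg: 0.0098 × 25 × 6 × 17 = 24.99, which is also wrong.

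**6. Effect on inference.** When units are used consistently, the same factor multiplies all three components in every patient. On simulated data with 110 patients per arm, dividing all values by 10 left both p-values unchanged (Mann-Whitney 3.66 × 10⁻⁶, t test 0.000296). A common factor also preserves ranks, each component's share of the total, and which patients lie above or below the median.

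**The case against.** A reader might infer that the trial's reported MP will be ten times too small. The article does not support that without conditions, for two reasons.

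- The factor and its direction depend on VT in litres and MP in J/min, and neither is stated. With millilitres the error runs the other way.
- The article defers to a cited method that is not shown, and the full protocol files, the case report form and the analysis code are not shown either. An error in the printed formula is established; an error in the derivation is not.

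A reader might also infer that the MP subgroup analysis or the between-arm tests are compromised. They are not: a common factor moves neither a median split nor a p-value, so nothing in section {20b} needs changing on this account. The outcome lists name MP only; the three components appear as a way of computing it. The scale can be corrected at any time from the recorded inputs.

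These objections narrow the point without removing it. No unit set used in the article makes 0.0098 correct. The same value stands in three separate equations, so a misread digit is an unlikely explanation. This is not a detail left to a fuller document either: the article states an explicit formula, and that formula is wrong as written.

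**Conclusion.** The point holds as an error in a printed outcome definition. The constant 0.0098 is inconsistent with cmH2O combined with either litres or millilitres, and the missing units leave the intended scale open. If the formulas are applied as printed, MP in J/min is ten times too small with VT in litres, and its elastic and PEEP terms are about 100 times too large with VT in millilitres. The damage is confined to absolute values and between-arm differences for one respiratory parameter within the secondary outcomes.

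The conversion itself needs no assumption. The inputs of the worked examples are assumed, but the factor of ten does not depend on them. That tests, ranks and component shares are unaffected does assume that volume units are consistent across VT, elastance and resistance.

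**What to change.** Replace 0.0098 with 0.098 in all three formulas. State the units beside them: VT in L, pressures in cmH2O, elastance in cmH2O/L, resistance in cmH2O/L/s, RR per minute, MP in J/min. Because VT is otherwise given per kg of PBW, say that the formulas take the absolute volume. Check that the derivation code uses the same constant and units, and report MP on that scale.

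The cost is one constant in three equations, a line of units and a check of the code. No new data are needed, and the conduct of the trial and the planned tests do not change.

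### The rescue-therapy outcome omits ECCOR, which the protocol itself names for persisting acidosis, and counts prone position, which it treats as standard care; as one any-use proportion it would be largely insensitive to an increase

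*Protocol article*

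**What the plan says.** The Objectives section of the protocol article sets out to test whether ultra-low tidal volume ventilation (ULTV) increases rescue therapy over the first 14 days. Under Secondary outcomes, item 7 defines the variable as "The use of rescue therapy (i.e., muscle relaxant, prone position, inhaled nitric oxide, recruiting maneuvers, ECMO) during the first 14 days after inclusion". ECCOR is not among the five therapies.

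The section on concomitant care {11d} introduces its list with "All ventilatory co-interventions will be standardized to ensure group comparability". That list contains:

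- Prone position: "Prone position will be advocated as long as PaO_2_/FiO_2_ < 150 mmHg", or while PEEP or FiO2 is above a stated level.
- Neuromuscular blocking agents (NMBA): "Neuromuscular blocking agent use will be advocated during the first 48 h of ARDS, in case of persisting severe hypoxemia" or asynchrony.
- ECCOR: "ECCOR will be considered in patients with persisting severe respiratory acidosis" that has not responded to the earlier measures.

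In Table 1, ECCOR or ECMO is the fifth and last step of the procedure for pH below 7.20. The Table 1 procedure for low oxygenation runs "1, use PP; 2, add NMBA; 3, add iNO; and 4, consider ECMO".

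The inclusion criteria require PaO2/FiO2 of 150 mmHg or less, and ventilation may not have begun more than 48 h before inclusion. Qualitative secondary outcomes are compared as event proportions by chi-square or Fisher's exact test.

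**The concern.** Two features of item 7 work against its objective.

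First, lowering tidal volume at a limited respiratory rate foreseeably raises PaCO2. The background section reports transient pH below 7.15 in 32% of the 34 pilot patients. If ULTV leads to more rescue, escalation for acidosis is one of the first places to look. A protocol-named escalation for that situation is absent from a closed list, so a patient who received ECCOR and none of the five listed therapies would count as not rescued. The trial is also described as testing ULTV without extracorporeal circulation, so ECCOR use in the ULTV arm is of direct interest.

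Second, prone position is described as standardized care for both arms in one section and as rescue in another. A therapy that nearly every enrolled patient qualifies for at entry cannot separate the arms on a yes/no basis. If it is pooled with rarer therapies, it can mask a difference in them.

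At stake is a secondary safety comparison in which a finding of no increase could say little about rescue. The primary outcome is unaffected.

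**Working it through.** The article gives no expected rate, target difference or power for this outcome, so there is no stated figure to reproduce. All rates of use below are assumptions, shown over a range.

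**Step 1: the list against the escalation steps.**

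| Therapy | In outcome 7 | Role elsewhere in the article |
|---|---|---|
| Prone position | yes | standardized care (11d); step 1 for low oxygenation (Table 1) |
| NMBA | yes | standardized care (11d), exact scope unclear; several Table 1 steps |
| Inhaled nitric oxide | yes | step 3 for low oxygenation (Table 1) |
| Recruitment maneuvers | yes | not recommended (11d) |
| ECMO | yes | last step for low oxygenation and, with ECCOR, for acidosis (Table 1) |
| ECCOR | **no** | last step for acidosis (Table 1); persisting acidosis (11d) |

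**Step 2: prone position against entry.** Entry requires PaO2/FiO2 ≤ 150 mmHg and prone position is advocated below 150 mmHg. On oxygenation alone, the two differ only for a patient at exactly 150 mmHg. Practically every patient in either arm therefore meets the indication at inclusion. Being indicated is not the same as being given, so the actual rate is unknown.

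**Step 3: size of the effect if pooled.** Let p be the share of patients with prone position or NMBA, equal in both arms, and q the share with nitric oxide or ECMO, independent of p. Then P(any) = 1 − (1 − p)(1 − q). Let q rise from 5% to 15%, a true increase of 10 points:

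| p | q = 5% | q = 15% | Difference |
|---|---|---|---|
| 90% | 1 − 0.10 × 0.95 = 90.5% | 1 − 0.10 × 0.85 = 91.5% | 1.0 point |
| 95% | 1 − 0.05 × 0.95 = 95.25% | 1 − 0.05 × 0.85 = 95.75% | 0.5 point |
| 98% | 1 − 0.02 × 0.95 = 98.1% | 1 − 0.02 × 0.85 = 98.3% | 0.2 point |

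**Step 4: power with 100 patients per arm**, the article's evaluable number, at two-sided 0.05, the level in its sample size section (two-proportion comparison).

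- Dilution: a rise from 15% to 30% in a rarer therapy has 72% power when compared alone. Pooled with background use of 80%, 90% or 95%, the totals are 83.0% vs 86.0%, 91.5% vs 93.0% and 95.75% vs 96.5%, with power of 8.5%, 5.9% and 4.6%.
- Ceiling: if ULTV halves the share of patients with no listed therapy, power is 27%, 15% and 8% at control rates of 90%, 95% and 98%.
- Extreme case: if every ULTV patient received a listed therapy, exact Fisher power would be 94%, 38% and 2% at those control rates.
- Compared separately: a rise from 5% to 15% in one therapy has 66% power, and from 5% to 10% has 27%.

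**The case against.** The strongest reply is that item 7 never defines a single any-use endpoint. It names five therapies, and neighbouring items also place several variables under one number: ten respiratory parameters, three classes of sedation drug, five types of adverse event. One proportion per therapy fits the statistical section equally well, and the choice could be left to an analysis plan that is not shown. This stands. A reader might infer that the outcome cannot show an increase at all, but the article supports that only under pooling. Compared separately, nitric oxide and ECMO are not at a ceiling.

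A reader might also infer that the main harm goes unseen. It does not. Severe mixed acidosis is part of outcome 8 and is collected daily to day 28 while patients are ventilated. Daily pH and PaCO2 are outcomes too, and ECMO, which shares the last acidosis step with ECCOR, is on the list. What is missed is the use of ECCOR itself.

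Two further inferences go too far:

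- Near-universal NMBA use depends on taking the first 48 h as an indication in its own right. The punctuation also allows a reading limited to severe hypoxemia or asynchrony. Table 1 mentions stopping NMBA after more than 48 h of administration, which hints at a routine course but does not settle it.
- The prone triggers in Table 1 and in section 11d look different but can both be followed. At PaO2 below 60 mmHg with FiO2 above 0.4, PaO2/FiO2 is already below 60/0.4 = 150 mmHg, so the Table 1 situation lies essentially within the general indication.

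Counting recruitment maneuvers although they are not recommended is also compatible with rescue use.

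The reply does not answer the ECCOR omission, because the article itself fixes a closed list. Nor does it answer the double role of prone position.

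**Conclusion.** The point holds in a limited form. Two parts rest on the text alone: the closed list omits an escalation that the article names twice for acidosis, and it counts as rescue a therapy advocated as standardized care at practically the entry threshold. The third part is conditional. If the outcome is analysed as one any-use proportion, it would be largely insensitive: a 10-point rise in nitric oxide or ECMO would appear as 0.2 to 1.0 points. That range assumes 90% to 98% background use, independence between therapies and equal background use in the arms; the article gives none of these. How far the ECCOR omission would change the counts cannot be said, because no expected frequency is given. This is a worthwhile, inexpensive improvement to a secondary outcome and not a threat to the trial's main conclusion.

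**What to change.** 1. Add ECCOR to the list in outcome 7.
2. State that each therapy is compared separately and that no single any-use proportion is the basis of the comparison.
3. Report prone position as number of sessions and NMBA as days of use, both to day 14, so that a difference in amount can be seen even if nearly all patients receive some.
4. Reconcile the concomitant care section with outcome 7 on whether prone position and early NMBA are standard care or rescue, and clarify the NMBA sentence. The triggers themselves are for the clinical team.

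The cost is mainly wording. Adherence to protocol procedures is already recorded daily for 14 days, but the case report form is not shown and must be checked for capture of ECCOR, prone sessions and NMBA days. The downside is more comparisons, each resting on few events. As the working shows, even separate comparisons will detect only large differences, so estimates with confidence intervals will be more useful than the tests.
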